### Outcomes

#### Primary outcome

The primary outcome will be total physical activity (counts per minute) of pupils at the end of the intervention (T2) measured using the Actigraph GT3X accelerometer (Actigraph LLC, Florida) worn for 7 days. The device will be placed on an elastic waist band and pupils will be asked to wear the accelerometer at all times, removing it only for bathing, water-based activities such as swimming and when asleep. Pupils will be asked to wear the accelerometer on their right hip and to ensure that it is worn in the same position each day. Pupils will be asked to wear the accelerometer for seven consecutive days and will be included in the analysis if they have ≥2 valid weekdays of data (500 mins/day) [72]. During measurement periods, pupils will be asked to keep a log of when they wore the accelerometer and took it off to encourage compliance with the wear-time protocol as recommended by Trost et al, 2005 [73]. Minutes of total physical activity (light, moderate and vigorous) per day will be estimated using the Evenson cut-points [74]. A sampling epoch of 15 s will be employed during data collection. Periods of ≥60 min of zero counts will be categorised as ‘non-wear’ and removed.

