#### Secondary outcomes

As outlined in Table 1, a number of secondary outcomes will also be assessed. It is also important to note, however, that there are no statistical power calculations for these assessments and as such all analyses will be presented with point estimates and 95% confidence intervals but without *p*-values. Accelerometer data will be used to calculate:
Total physical activity (counts per minute) at mid-intervention (T1) and follow up (T3)Time spent in sedentary behaviour and light, moderate and vigorous intensity physical activity [74] at mid-intervention (T1), end of intervention (T2) and follow up (T3)Proportion of pupils meeting current physical activity recommendations [6] at mid-intervention (T1), end of intervention (T2) and follow up (T3)

The following secondary outcomes will be measured at baseline (T0), end of intervention (T2) and follow up (T3) to assess between group differences and changes over time:

Height (cm) and weight (kg) will be measured to the nearest 0.1 cm and 0.1 kg, respectively, using a freestanding stadiometer (Leicester Height Measure), and digital scales (Seca 877) to calculate body Mass Index (BMI). BMI will be converted to an age-specific and gender-specific z-score [75, 76]Waist and hip circumference will be measured to the nearest 0.1 cm using an anatomical measuring tape and waist-to-hip ratio will be calculated.Coping, resilience and cognitive reappraisal [55]Sleep quality, duration and efficiency (The Pittsburgh Sleep Quality Index) [56]Social media use, social integration and emotional connection to social media [57, 58]Body weight and appearance satisfaction [59]

At baseline (T0) the following descriptive data will be collected:
Date of birthHome postcode/Eircode to derive Index of Multiple Deprivation (IMD)

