#### Quantitative analysis

Outcome data will be reported in accordance with Consolidated Standards of Reporting Trials (CONSORT) guidelines [78]. The statistician performing the data analyses ([name]) will be blinded to allocation throughout the study and statistical analysis will only be undertaken when all data has been collected (T3). Pupils will be included in the analysis regardless of compliance with the physical activity intervention. We will apply a multilevel statistical model using ML- win [79] to assess changes in total physical activity (mins per week) from baseline to post-intervention. Multilevel modelling will also be used for the change in total physical activity at other timepoints and secondary continuous outcomes adjusting the false discovery rate using the Benjamini-Hochberg Procedure [80]. Outcomes will be compared between the control and intervention groups using a 2-level multilevel model, with pupils nested within schools. The models will be adjusted for the child-level covariates (level 1): baseline total physical activity (minutes per week), age and BMI z-score; and the following school-level covariates (level 2): social economic status (postcode/Eircode). In the interests of parsimony, covariates will only be retained if their inclusion results in a significant improvement in fit statistics.

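### Accelerometer outcomes in minutes are not scaled to wear time, and the analysis model brings this into the main comparison by using minutes per week instead of the stated counts per minute

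*Protocol article*

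**What the plan says.** All places are in the protocol article.

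- **Primary outcome, metric.** "The primary outcome will be total physical activity (counts per minute) of pupils at the end of the intervention (T2"). The same unit is used for total activity at T1 and T3 under Secondary outcomes.
- **Primary outcome, valid data.** Pupils are "included in the analysis if they have ≥2 valid weekdays of data (500 mins/day"). The 500 min is a floor, and no ceiling or standard day is stated. Pupils are asked to wear the device through all waking hours except for bathing and water activities. "Periods of ≥60 min of zero counts will be categorised as" non-wear and taken out.
- **Primary outcome, minutes.** "Minutes of total physical activity (light, moderate and vigorous) per day will be estimated using the Evenson cut-points".
- **Secondary outcomes.** "Time spent in sedentary behaviour and light, moderate and vigorous intensity physical activity" at T1, T2 and T3, stated as time and not as a share of wear.
- **Quantitative analysis.** The multilevel model is to "assess changes in total physical activity (mins per week) from baseline to post-intervention". The pupil-level covariates are "baseline total physical activity (minutes per week), age and BMI z-score", and the school-level covariate is socioeconomic status. A covariate stays only if it significantly improves fit, so the list can shrink but has no route by which wear time would enter.
- **Sample size calculations.** The target is 11.41 min/day of total activity with an SD of 25 min.

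**The concern.** Once non-wear is removed, counts per minute is a rate per worn minute, so longer wear does not by itself raise it. Minutes behave differently. A pupil who wears the device longer accumulates more active minutes and more sedentary minutes with no change in behaviour. Baseline minutes in the model do not correct for this, because they carry wear at T0 and not wear at follow-up.

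Two things are at stake. First, the main analysis: if the model is run as Quantitative analysis describes it, the wear-scaled primary metric is replaced by one that is not scaled. Second, the Background hypothesises that walking will replace sedentary time. Sedentary minutes take up whatever part of extra wear is not active. Longer wear in the intervention arm could therefore hide a real substitution, and shorter wear could imitate one. A difference in wear is conceivable, since walks before school might lead intervention pupils to put the device on earlier, but the article gives no data on this.

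**Working it through.** **1. The plan's own figure.** Inputs from Sample size calculations: difference 11.41 min, SD 25 min, power 80%, alpha 0.05 (taken as two-sided), cluster size 20, ICC 0.03, coefficient of variation 0.46.

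- Pupils per arm without clustering: 2 × (25 × (1.960 + 0.842) / 11.41)² = 75.4, so 76.
- Design effect: 1 + ((1 + 0.46²) × 20 − 1) × 0.03 = 1.697.
- Schools, normal approximation: 2 × 76 × 1.697 / 20 = 12.9.
- With a noncentral t on 13 degrees of freedom, 15 schools give power 0.799.

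The stated 15 schools are reproduced, and the calculation is in unscaled minutes per day.

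**2. Units side by side.**

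| Place | Quantity | Scaled to wear? |
|---|---|---|
| Primary outcome | Total activity at T2, counts per minute | Yes |
| Secondary outcomes | Total activity at T1 and T3, counts per minute | Yes |
| Secondary outcomes | Sedentary, light, moderate, vigorous time | Not stated |
| Quantitative analysis | Total activity, minutes per week | Not stated |
| Quantitative analysis | Baseline covariate, minutes per week | Not stated |
| Sample size calculations | 11.41 min/day, SD 25 min | Not stated |

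**3. How wear enters a minutes outcome.** Let f be the share of worn time that is light, moderate or vigorous. The article does not give f, so 25–45% is assumed. With behaviour unchanged, a wear gap of w min/day shifts active time by f × w and sedentary time by (1 − f) × w, both with the same sign.

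- Two pupils with the same f, one with 500 min of wear and one with 700 min: active time differs by 200 × 0.25 = 50 to 200 × 0.45 = 90 min, and sedentary time by 150 to 110 min. These are individual days, not arm means.
- Each 10 min/day of gap between arm means: 2.5 to 4.5 min of activity (22% to 39% of 11.41) and 7.5 to 5.5 min of sedentary time.
- Gap that alone produces the target: 11.41 / 0.45 = 25.4 min/day to 11.41 / 0.25 = 45.6 min/day. Sedentary time then moves by 25.4 × 0.55 = 14.0 to 45.6 × 0.75 = 34.2 min/day in the same direction.

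A rate per worn minute, or a percentage of wear, is unchanged by this proportional shift. It does not remove an effect that arises because the extra worn minutes differ in intensity from the rest.

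**The case against.** **The primary outcome is already scaled.** A reader might infer that the trial's primary outcome ignores wear. It does not: counts per minute is normalised at T2, and also at T1 and T3. This stands in full. The main analysis is affected only because Quantitative analysis names a different unit. If that is settled in favour of counts per minute, what remains is secondary outcomes, which are unpowered and to be reported as estimates with intervals and without p-values. A shifted estimate would still mislead there.

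**No difference in wear by arm is shown.** A reader might infer that the results will be biased. The documents do not support that. All pupils get the same wearing instruction and the same log, and the incentive for returning the device does not distinguish arms. This also stands, so any bias is conditional.

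**Chance imbalance in wear is not an extra harm.** It is tempting to add a random wear difference on top. Ordinary variation in wear is already inside the 25 min SD, and so inside the power calculation and the confidence intervals. Large assumed values also clash with that SD: a wear SD of 90 min at a 35% active share implies 31.5 min from wear alone, more than the whole 25 min. With 9 schools of 19 pupils per arm (171), the full 95% range for activity is 1.96 × 25 × √(2 × 1.70 / 171) = ±6.9 min, wear included.

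**Details may sit in a fuller document.** How valid days are averaged or scaled up to a week is commonly left to a full protocol or SAP and is not criticised here. The article does, however, state its own model unit and covariate list, and those can be judged as written.

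**Conclusion.** The point holds for the outcomes expressed in minutes: sedentary, light, moderate and vigorous time, and total activity as modelled in minutes per week together with its baseline covariate. It does not hold for the counts-per-minute outcomes. The main analysis is exposed only through the conflict between Primary outcome and Quantitative analysis, which must be reconciled.

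The size is conditional. At an assumed active share of 25–45%, with behaviour unchanged, a gap in mean wear of about 25–46 min/day would match the 11.41 min/day target, and smaller gaps scale in proportion. Sedentary time would move the same way, against the substitution the hypothesis predicts. The documents give no wear mean, SD or arm difference, so whether any gap will occur is unknown. If there is none, the consequence is some loss of precision, whose amount cannot be estimated from the article. The plan should be changed on this point, but it does not make the stated primary outcome invalid.

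**What to change.** - In Quantitative analysis, model the primary outcome in counts per minute, in line with Primary outcome, with the baseline covariate in the same unit.
- Analyse each minutes outcome and its baseline as a percentage of valid wear time, or as minutes per standardised wear day.
- Report valid wear time by arm at each time point.
- As a sensitivity analysis, model raw minutes with wear time as a covariate that is exempt from the fit-based retention rule.

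**Cost.** Only the analysis wording changes; wear must already be computed to apply the 500 min rule. Percentages are less direct to read than minutes, which conversion back to a standard day largely solves. Follow-up wear is measured after randomisation, so if the intervention itself changes wear, adjusting for it conditions on a consequence of treatment; adjusted and unadjusted results should be shown together. The sample size stays in minutes per day, so the text should acknowledge that power was derived in a different unit from the primary model.

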#### Secondary outcomes

As outlined in Table 1, a number of secondary outcomes will also be assessed. It is also important to note, however, that there are no statistical power calculations for these assessments and as such all analyses will be presented with point estimates and 95% confidence intervals but without *p*-values. Accelerometer data will be used to calculate:
Total physical activity (counts per minute) at mid-intervention (T1) and follow up (T3)Time spent in sedentary behaviour and light, moderate and vigorous intensity physical activity [74] at mid-intervention (T1), end of intervention (T2) and follow up (T3)Proportion of pupils meeting current physical activity recommendations [6] at mid-intervention (T1), end of intervention (T2) and follow up (T3)

The following secondary outcomes will be measured at baseline (T0), end of intervention (T2) and follow up (T3) to assess between group differences and changes over time:

Height (cm) and weight (kg) will be measured to the nearest 0.1 cm and 0.1 kg, respectively, using a freestanding stadiometer (Leicester Height Measure), and digital scales (Seca 877) to calculate body Mass Index (BMI). BMI will be converted to an age-specific and gender-specific z-score [75, 76]Waist and hip circumference will be measured to the nearest 0.1 cm using an anatomical measuring tape and waist-to-hip ratio will be calculated.Coping, resilience and cognitive reappraisal [55]Sleep quality, duration and efficiency (The Pittsburgh Sleep Quality Index) [56]Social media use, social integration and emotional connection to social media [57, 58]Body weight and appearance satisfaction [59]

At baseline (T0) the following descriptive data will be collected:
Date of birthHome postcode/Eircode to derive Index of Multiple Deprivation (IMD)

### Process evaluation

A mixed-methods process evaluation will be undertaken. At baseline (T0), end of the intervention (T2) and follow up (T3), pupils (aged 12-14 years) will be asked to complete a series of validated questionnaires to assess self-efficacy for physical activity and walking [60], health-related quality of life [61], reasons for engaging in physical activity [62, 63]. Friendship nominations will be assessed at baseline (T0) and at the end of the intervention (T2) to determine the effect of social networks on physical activity behaviour and intervention engagement. This will involve each pupil nominating school friends who are also participants in the current study. The number of friends to nominate will not be specified, although 10 lines will be provided on the form. Friendship networks will be constructed from these nominations [77].

At baseline (T0), focus groups will be conducted in all schools and pupils will be randomly invited to participate. The aim of these focus groups is to investigate pupils’ motivation for physical activity, barriers to physical activity and the influence of social media usage on their physical activity. At the end of the intervention (T2), high and low attendees from the intervention schools will be invited to take part in focus group discussions. These focus group sessions will enable pupils to share their experience of the WISH trial and assess any changes in behaviour pre- and post-intervention. The focus groups will also seek to identify factors that affected participation, motivation and enjoyment of the intervention.

The fidelity of each walk will be assessed through a self-report checklist completed by walk leaders. This will note attendees and assess walk duration and location (indoor/outdoor). To assess how elements of the environment may have affected delivery of the intervention interviews will be conducted with walk leaders. These interviews will be conducted at the end of the intervention (T2). Walk leaders will be asked to complete a brief set of questionnaires at baseline (T0) and end of the intervention (T2) to assess self-perception of physical activity and fitness [64], physical activity self-efficacy [65], physical activity enjoyment [66] and leadership skills [67] to profile the characteristics of those pupils who volunteer as walk leaders.

In addition, an in-depth interview will be held with one school contact (e.g. Head of Key Stage 3 / Head of Year or equivalent) per intervention school at the end of the intervention (T2) to identify key elements that might have affected implementation. Any adverse events will be recorded and reported to the Chair of the Trial Steering Committee and the Chair of the Ethics Committee.

### Data analysis

Data will be entered electronically on a secure file storage system and password protected. Data will be anonymised by assigning a unique identification number to each pupil.

#### Quantitative analysis

Outcome data will be reported in accordance with Consolidated Standards of Reporting Trials (CONSORT) guidelines [78]. The statistician performing the data analyses ([name]) will be blinded to allocation throughout the study and statistical analysis will only be undertaken when all data has been collected (T3). Pupils will be included in the analysis regardless of compliance with the physical activity intervention. We will apply a multilevel statistical model using ML- win [79] to assess changes in total physical activity (mins per week) from baseline to post-intervention. Multilevel modelling will also be used for the change in total physical activity at other timepoints and secondary continuous outcomes adjusting the false discovery rate using the Benjamini-Hochberg Procedure [80]. Outcomes will be compared between the control and intervention groups using a 2-level multilevel model, with pupils nested within schools. The models will be adjusted for the child-level covariates (level 1): baseline total physical activity (minutes per week), age and BMI z-score; and the following school-level covariates (level 2): social economic status (postcode/Eircode). In the interests of parsimony, covariates will only be retained if their inclusion results in a significant improvement in fit statistics.

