## Methods

### Study design

The WISH study is a school-based clustered randomised controlled trial (c-RCT). The design of the project was informed by a feasibility pilot study [50] that used the Medical Research Council (MRC) [51] framework for complex interventions to develop a peer-led walking intervention. Specifically, following a systematic review of walking interventions in children and adolescents [31], focus groups were conducted to explore the attitudes of adolescents towards physical activity [37]. The findings of both the systematic review and focus groups were used to inform the design of the peer-led, school-based walking intervention [50] based on the socioecological framework and informed by Self-Determination Theory (SDT), which provides a framework for understanding and enhancing the motivational mediators of behaviour change [52–54].

Eighteen post-primary schools will be recruited across the Border Region of Ireland / Northern Ireland. Following completion of baseline data collection, schools will be randomised using a 1:1 allocation. Study outcomes will be assessed at four timepoints: baseline (T0), mid-intervention (T1), end of intervention (T2) and follow up (T3) as outlined in Fig. 1. A mixed-methods process evaluation will be undertaken at baseline and at the end of the intervention. Table 1 provides an overview of data collection and outcome measures, the details of which are provided below.

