### Sample size calculations

Sample size calculations are based on the WISH feasibility trial [50], which detected a mean difference of 11.41 min in total physical activity (light, moderate and vigorous intensity physical activity) measured using accelerometery between the intervention (2 schools consisting of a total of 79 children) and control (4 schools consisting of 84 children in total) groups. In order to detect a difference of 11.41 min total physical activity per day between groups, assuming a standard deviation (SD) (pooled intervention and control group SD) of 25 min in total physical activity, a power of 80%, a significance of 0.05, an average cluster size of 20 children, an intra-class correlation of 0.03 (calculated from pilot data [50]), and a coefficient of variation of 0.46, the sample size needed is 15 schools increasing to 16 schools (8 per study arm) to allow for 10% cluster attrition. To allow for 20% loss to follow up we will recruit at least 24 children per cluster (at least 384 children in total). Based on recruitment rates of 34% in our feasibility study [50], all schools that have at least 80 girls across years 9–10 (Northern Ireland) or total enrolment of > 240 girls (Ireland) will be eligible to participate in the study. From the Northern Ireland School Census [68] we estimate that 77 schools meet these criteria and based on 2016 school recruitment data for Ireland [69] 54 post-primary schools meet these criteria.

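### One baseline covariate, total activity in minutes per week, serves every model, so most secondary continuous outcomes are not adjusted for their own baseline value

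*Protocol article*

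**What the plan says.** All of this is in the protocol article.

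- **Primary model.** Quantitative analysis describes a multilevel model "to assess changes in total physical activity (mins per week) from baseline to post-intervention".
- **Other models.** The next sentence extends the approach: "Multilevel modelling will also be used for the change in total physical activity at other timepoints and secondary continuous outcomes".
- **Covariates.** One list then follows for these models: "The models will be adjusted for the child-level covariates (level 1): baseline total physical activity (minutes per week), age and BMI z-score", with socioeconomic status at school level. Nothing says that the baseline term changes with the outcome.
- **Retention.** The same section adds that "covariates will only be retained if their inclusion results in a significant improvement in fit statistics".
- **Baseline data.** Study design states: "Study outcomes will be assessed at four timepoints: baseline (T0), mid-intervention (T1), end of intervention (T2) and follow up (T3". For the non-accelerometer outcomes, Secondary outcomes states: "The following secondary outcomes will be measured at baseline (T0), end of intervention (T2) and follow up (T3". Table 1 marks a T0 measurement for each.
- **Primary outcome unit.** The Primary outcome section states: "The primary outcome will be total physical activity (counts per minute) of pupils at the end of the intervention (T2". This is not the unit used in Quantitative analysis.

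**The concern.** In a randomised comparison of a continuous outcome measured before and after, the outcome's own baseline is usually the most useful covariate. It removes the most residual variance and corrects the estimate for chance differences between arms at the start. Read as written, the model for sleep quality would contain baseline activity minutes but not baseline sleep quality, although that value is on file.

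Two features of this trial make the choice matter. Secondary outcomes are to be reported as point estimates with 95% confidence intervals and no p-values, so interval width and freedom from baseline imbalance are what the reader relies on. And only nine schools per arm are randomised, stratified by country alone, so some imbalance in baseline means is to be expected.

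The retention rule adds to the problem. For an outcome weakly related to activity, the single baseline term may be dropped, leaving no baseline covariate at all.

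**Working it through.** **1. The plan's own figure.** Sample size calculations sets its target thus: "In order to detect a difference of 11.41 min total physical activity per day between groups", with SD 25, 80% power, significance 0.05 (taken as two-sided), cluster size 20, ICC 0.03 and coefficient of variation 0.46.
- Per arm before clustering: 2 × (25 × 2.802 / 11.41)² = 75.4.
- Design effect: 1 + ((1 + 0.46²) × 20 − 1) × 0.03 = 1.697.
- 75.4 × 1.697 = 127.9 pupils, or 6.39 schools per arm. Adding one school per arm as a small-sample correction gives 2 × 7.39 = 14.8, so 15 schools, as stated.

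No baseline-adjustment term enters, so this figure does not depend on the point.

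**2. Which models contain their own baseline.**

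| Outcome | Own T0 value in the list? |
|---|---|
| Total activity, minutes per week | Yes |
| BMI z-score | Probably (timing of the covariate not stated) |
| Total activity, counts per minute | No, different scale |
| Sedentary, light, moderate, vigorous time | No, but related to the listed term |
| Waist:hip ratio, sleep, emotion regulation, social media use, body satisfaction | No |

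**3. Loss of precision when the listed covariate is nearly unrelated to the outcome.** Let r be the correlation between an outcome's baseline and follow-up values, with equal SD at both times. The article gives no r, so 0.3 to 0.8 is assumed. Relative to the raw follow-up variance, the pupil-level variance is 1−r² with own-baseline adjustment, 2(1−r) for a change score and 1 for a follow-up score. The ratios to own-baseline adjustment are:

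| r | Change score, 2/(1+r) | Follow-up score, 1/(1−r²) |
|---|---|---|
| 0.3 | 1.54 | 1.10 |
| 0.5 | 1.33 | 1.33 |
| 0.7 | 1.18 | 1.96 |
| 0.8 | 1.11 | 2.78 |

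**4. Loss when the listed covariate is related to the outcome.** Suppose baseline minutes correlate a with the outcome's own baseline and relate to follow-up only through it. The ratios become [2(1−r) − a²(1−r)²]/(1−r²) for change and (1−a²r²)/(1−r²) for follow-up.
- For a = 0.8 to 0.95, a plausible range for counts per minute: at r = 0.5, 1.12 to 1.03 either way; at r = 0.7, 1.06 to 1.02 (change) or 1.35 to 1.09 (follow-up).
- For a = 0.5: 1.25 at r = 0.5; at r = 0.7, 1.13 (change) or 1.72 (follow-up).

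**5. Effect of chance imbalance.** If the arms differ at baseline by D, and the listed covariate does not pick this up, the estimate is shifted by (r−1)D for a change score, by rD for a follow-up score, and by 0 with own-baseline adjustment. For a sense of D, take 18 schools of 20 pupils and borrow the design effect above: the standard error of the baseline difference is √(2 × 1.697/180) = 0.137 SD. An imbalance of that size shifts a change-score estimate by −0.069 SD at r = 0.5 and −0.041 SD at r = 0.7. It shifts a follow-up estimate by 0.069 and 0.096 SD.

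**6. From pupil-level variance to the treatment effect.** With the same ICC and cluster sizes, the design effect splits into 0.97 (pupils) and 0.727 (schools). If the school part were the same under both methods, the change-score ratio would fall to (0.97 × 1.0 + 0.727)/(0.97 × 0.75 + 0.727) = 1.697/1.4545 = 1.17 at r = 0.5, and to (0.97 × 0.6 + 0.727)/(0.97 × 0.51 + 0.727) = 1.309/1.222 = 1.07 at r = 0.7. This is an illustration only: the ICC of 0.03 is for total activity minutes, and adjustment may also change the school part.

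**The case against.** The strongest reply is that the list was written for the total activity model and fits it: in minutes per week, the covariate is that outcome's own baseline. A reader might infer from the shared list that no model has its own baseline. The documents do not support that, for total activity as Quantitative analysis words it or, probably, for BMI z-score.

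A reader might also infer that baseline imbalance goes wholly uncorrected. That is not supported either. The section speaks of changes from baseline, and a change score subtracts the own baseline; its fault is over-correction, by (r−1) times the imbalance. Whether the word change covers the secondary outcomes as well as total activity is unclear, so both cases are shown above.

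Third, the counts-per-minute mismatch follows from a separate contradiction over the primary outcome's unit; if minutes per week is chosen, it disappears. Fourth, the largest ratios need follow-up scores and an unrelated covariate. That does not suit intensity-specific time, since light, moderate and vigorous minutes make up the total. Fifth, the affected secondary outcomes are unpowered, and randomisation keeps estimates unbiased on average over allocations. All of this stands and limits the size of the point.

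The argument that such detail belongs in an analysis plan does not stand. The article names a specific covariate and unit and applies it to the models, so it states a choice.

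**Conclusion.** The point holds for secondary continuous outcomes other than total activity and BMI z-score, and for the primary outcome only if it is analysed in counts per minute. It is clearest for waist:hip ratio and the questionnaire outcomes, where baseline activity is likely to be a weak substitute. Under change scores, the more natural reading, their pupil-level variance is up to about 1.33 times (r = 0.5) or 1.18 times (r = 0.7) that of own-baseline adjustment, which widens intervals by about 15% or 8% at most (√1.33 = 1.15; √1.18 = 1.08). For counts per minute the loss is small to moderate.

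These sizes rest on assumed correlations, equal SDs over time and a baseline covariate nearly unrelated to the outcome. They describe pupil-level variance, so the effect on the treatment comparison may be smaller. The sample size and the validity of the randomised comparison are not in question. What is lost is precision, and correction for imbalance, that data already collected would provide.

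**What to change.** In Quantitative analysis, replace the baseline activity term by the T0 value of the outcome being analysed, on the same scale, in every continuous-outcome model, together with age and BMI z-score. State that this term is always kept and is exempt from the rule that drops covariates without a significant improvement in fit; otherwise the new term could be removed again. Baseline total activity may stay as an additional covariate for non-activity outcomes.

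State one unit for the primary outcome and use it in both the Primary outcome and Quantitative analysis sections, so that the outcome and its baseline match.

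The cost is a few words. No new data are needed, and since analysis starts only after T3 with a blinded statistician, the change can be made before any results are seen.
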